#### Hospitalisation

At each contact, participants will be asked to report hospitalisation that occurs for any reason during the 24-week study period.

#### Serum inflammatory markers

(Baseline, 12 weeks, and 24 weeks): At these time points, 20 ml of blood will be collected from participants. Prior to assay, the blood will be centrifuged as per standard operating procedures and frozen at −80 °C for storage. Assays of inflammatory markers and cytokines will assess interleukin (IL)-1β, IL-2, IL-4, IL-5, IL-6, IL-10, IL-12, IL-13; IFN-γ; TNF-α; and, possibly, MCP1; CRP; and P-selectin (subject to costs).

A schematic of the ASPiVLU trial design is provided in Fig. 1, and an overview of the study schedule is provided in Table 1. The CONSORT flow diagram is provided in Fig. 2.

**Fig. 1 Fig1:**
[figure not shown]
Schematic of the Aspirin in Venous Leg Ulcer trial (ASPiVLU) design

**Table 1 Tab1:** Study schedule

Measurement/activity	Screening^a^	Treatment period in weeks													Follow-up period	
		*(Weekly wound management and assessments until target ulcer healed OR 12 weeks – whichever occurs first. The 12-week visit is mandatory for all participants regardless of ulcer status.)*													*(from week 12 until week 24)*	
		Recruitment & Baseline Assessment (Day 1)	Wk 1	Wk 2^b^	Wk 3^b^	Wk 4^b^	Wk 5^b^	Wk 6^b^	Wk 7^b^	Wk 8^b^	Wk 9^b^	Wk 10^b^	Wk 11^b^	Wk 12	Monthly	Wk 24/end of study
Informed consent		X														
Eligibility criteria	X															
Recruitment & randomisation		X														
Target ulcer assessment – general features		X	X	X	X	X	X	X	X	X	X	X	X	X^3^		
Wound pain score		X	X	X	X	X	X	X	X	X	X	X	X	X^3^	X	X
Target ulcer assessment – size (tracing) & photo		X				X				X				X^3^		
Medical history including demographics & medications		X														
Physical examination including vital signs		X														
QOL assessment (EQ-5D-5L)		X												X		X
Serum sample		X												X		X
Trial medication dispensed		X														
Ulcer care education		X														
Adherence to compression (or hosiery)			X	X	X	X	X	X	X	X	X	X	X	X	X	X
Adherence to trial medication			X	X	X	X	X	X	X	X	X	X	X	X	X	X
Concomitant/new medication			X	X	X	X	X	X	X	X	X	X	X	X	X	X
Adverse events including hospitalisation			X	X	X	X	X	X	X	X	X	X	X	X	X	X
Wound assessment			X	X	X	X	X	X	X	X	X	X	X	X		
Ulcer prevention education			X^2^	X^2^	X^2^	X^2^	X^2^	X^2^	X^2^	X^2^	X^2^	X^2^	X^2^	X		
Target ulcer recurrence assessment															X^2^	X^2^
Refer to wound clinic														X^3^	X^4^	X^4^
Reconciliation of medication																X

^a^Screening to be conducted within 14 days of baseline (day 1) assessment

^b^Assessment conducted only if the target ulcer unhealed

X^2^ = if healed

X^3^ = if not healed

X^4^ = if ulcer has recurred *(this applies to participants whose target ulcer recurs after initial healing is achieved)*

**Fig. 2 Fig2:**
[figure not shown]
The Aspirin in Venous Leg Ulcer (ASPiVLU) trial flow diagram

### Participation discontinuation

If a participant withdraws from the study, the reason will be documented, and the participant will be referred for routine care to the wound clinic, if required. Participants will be asked to allow measurement of the target ulcer at routine treatment visits for ascertainment of outcomes. Participants unwilling to continue participation during the follow-up period will be asked for permission to allow investigators to collect information from their medical records.

### Follow-up of participants ‘off protocol’

‘Off protocol’ is defined as those *study participants who cease trial medications on clinical grounds or commence on aspirin therapy for other reasons*. This may be short-term or for the remainder of the study. Regardless of the decision to continue with study medication, these participants will be asked to participate in all scheduled follow-up contacts, as if they were maintaining full participation. Those who are unwilling or unable to do this will be asked to agree to phone call or mail follow-up, and/or permission for study staff to continue surveillance of their clinical records.

### Sample size

We estimate that 268 participants will be required. Based on a previous compression bandaging study, we expect 50 % of ulcers to have healed at 12 weeks in the placebo group [15]. Aspirin is expected to increase this additively by 20 %; that is, we expect 70 % of the aspirin group to be healed at 12 weeks [20, 22]. Twelve-week survival rates of 0.5 and 0.3 in the placebo and aspirin groups, respectively, translate to cumulative hazard rates of 0.7 and 1.2, respectively, and a hazard ratio of 1.74. For 90 % power to detect this hazard ratio in a two-sided (alpha = 0.05) test for time to healing, analysed by a log-rank test, we require 121 people per group. Allowing for 10 % loss to follow-up, we will recruit *n* = 134 participants per group. With this sample size, and the same assumptions about percentage healed, we have 87 % power for a two-sample test of the proportion healed at 12 weeks.

For the secondary outcome of healed at 12 weeks and recurrence free at 24 weeks, we anticipate 60/121 (approximately 50 %) in the placebo group to be healed at 12 weeks and 85/121 (approximately 70 %) in the aspirin group to be healed. Of these participants with healed ulcers, in the placebo group, we expect 24 (40 % of 60) to recur by 24 weeks from baseline, i.e. 36/121 to be healed at 12 weeks and recurrence free at 24 weeks. We have 90 % power to detect a difference between the placebo and aspirin groups if the proportion healed at 12 weeks and recurrence free at 24 weeks in the aspirin group is 51 % (*n* = 62) of 121 participants.

### Data management and statistical analyses

Results from the trial assessments will be recorded in the electronic case report forms (CRF) via an electronic data capture (EDC) system. The REDCap EDC system is a secure, web-based system that is available for free to institutional partners (www.projectredcap.org). Each clinical site will have a unique password and will enter data directly into the EDC system via a tablet supplied by the ASPiVLU trial.

The primary and secondary outcomes will be analysed according to intention-to-treat principles, i.e. by the treatment to which they were randomised. The primary outcome will be analysed with a log-rank test to compare the time to healing, up to the 12-week time point, i.e. with censoring at 12 weeks, between the two randomised treatment groups. A secondary analysis of the primary hypothesis will use logistic regression to compare between groups the proportion of participants healed by 12 weeks. The secondary outcome, the proportion of patients healed by 12 weeks and remaining recurrence-free at 24 weeks, will be compared between the two groups using logistic regression. The levels of inflammatory markers in the plasma will be compared between groups using a linear mixed model with a random effect for participants to allow for correlation among each individual’s repeat measures over time, adjustment for the biomarker’s level at randomisation, and an interaction between the time since randomisation and the randomisation group. The secondary outcomes of pain score and EQ-5D-5L will be analysed in linear mixed models, with a random effect for participant, an adjustment for the measure at randomisation, and an interaction between the time since randomisation and the randomisation group.

A secondary set of analyses will be performed to adjust for two predictors of healing: (1) ulcer area and ulcer duration at baseline and (2) any baseline characteristics that are found to be imbalanced between the groups to the extent of a 0.25 standard deviation difference in means (quantitative measures) or an odds ratio of 1.5 (binary measures). For time to healing these secondary analyses will use a Cox proportional hazards regression.

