### Study setting and participants

The study population consists of adult patients living in Australia. The study is being conducted in four states (Victoria, New South Wales, Queensland, and Tasmania). Potential participants will be identified from community nursing settings, general practice clinics, and hospital outpatient wound clinics. All eligible patients will be identified at six participating ASPiVLU study wound clinics and offered study participation.

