### Allocation concealment and implementation

The study medication will be packaged in identical containers. Each container will be pre-labelled (by an independent drug-packaging group contracted to provide the study medication) with a study identifier according to the randomisation schedule. Allocation will be stratified by wound clinic and wound size as measured by the Margolis index [10]. The Margolis index is a prognostic score for venous ulcer healing derived from dichotomous categorisations of the ulcer area and duration of the current ulcer. Hence, stratification aims to avoid baseline imbalances in the ulcer size and duration, which are highly predictive of outcome. Stratification based on clinic site will avoid variance in any baseline characteristics related to the geographical location or local clinical practice. The study investigators and the research nurses distributing the medication and assessing outcomes will remain blind to the treatment allocation.

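### The primary log-rank test names none of the randomisation strata: it is valid, but conservative and less efficient than a log-rank stratified by Margolis index, which costs nothing

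*Protocol article*

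**What the plan says.** Under Allocation concealment and implementation, the protocol states: "Allocation will be stratified by wound clinic and wound size as measured by the Margolis index". It describes the index as built from two-way splits of ulcer area and duration, and gives the reason: "stratification aims to avoid baseline imbalances in the ulcer size and duration, which are highly predictive of outcome". Clinic is added to balance location and local practice. Study setting and participants gives the number of sites: "All eligible patients will be identified at six participating ASPiVLU study wound clinics".

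Under Data management and statistical analyses, the primary test is fixed as follows: "The primary outcome will be analysed with a log-rank test to compare the time to healing, up to the 12-week time point". The comparison is between the two randomised groups, with censoring at 12 weeks, and no stratum is named. The prognostic factors appear later: "A secondary set of analyses will be performed to adjust for two predictors of healing: (1) ulcer area and ulcer duration at baseline", together with any baseline characteristic found imbalanced beyond a stated threshold. The method is then given: "For time to healing these secondary analyses will use a Cox proportional hazards regression". Clinic is not named in any analysis.

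The Sample size section rests on a plain two-group log-rank test.

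**The concern.** Stratified allocation removes most of the chance imbalance in the stratifying factors. A log-rank test that ignores those factors still uses a variance that allows for such imbalance. When the factors are strongly prognostic, that variance is too large and the test rejects less often than its nominal level. Leaving out a strong prognostic factor also pulls the overall hazard ratio towards 1, relative to the hazard ratio within strata.

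The protocol's Background suggests that the contrast is large. It gives about 70% healed by 24 weeks for smaller, newer ulcers and 20% for larger, older ones. Both kinds are eligible: the area limit is 20 cm² against a prognostic cut at 10 cm², and duration has no upper limit. At stake is power that the stratified design makes available and the primary analysis does not use.

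**Working it through.** **1. The plan's own figure.** The inputs are from the Sample size section: "we expect 50 % of ulcers to have healed at 12 weeks in the placebo group", 70% with aspirin, two-sided alpha 0.05 and 90% power.
- Hazard ratio = ln(0.3)/ln(0.5) = 1.204/0.693 = 1.737, stated as 1.74.
- Events by Freedman's formula = (1.960 + 1.282)² × [(1 + 1.737)/(1.737 − 1)]² = about 145.
- Participants = 145/0.6 = 241.7, or 120.8 per group, which rounds up to the stated 121. (Schoenfeld's formula gives 138 events and 115 per group.)
- Loss to follow-up: 121/0.9 = 134.4, against the stated 134.

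The sample size is therefore reproduced for the unstratified test that the plan names.

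**2. How strong the prognostic contrast may be.** From the Background's 24-week figures, the cumulative hazards are −ln(0.3) = 1.204 and −ln(0.8) = 0.223, a ratio of about 5.4. These rates cannot be carried directly to 12 weeks. Under a constant hazard the better group would be at 1 − √0.3 = 45%, already below the 50% assumed for placebo overall. The 12-week stratum rates and the mix of strata are therefore assumptions, chosen to average close to 50%.

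**3. Simulation.** Each trial had 121 per arm, healing assessed weekly, censoring at 12 weeks, six clinics and permuted blocks of 4 within clinic-by-Margolis cells. There were 1,500 replicates per scenario (Monte Carlo standard error about 0.4 to 1.1 points). The tests were applied to the same simulated trials. The table shows power with HR 1.74 within every stratum.

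| Placebo healed at 12 weeks by stratum (mix) | Overall aspirin rate | Unstratified | By Margolis | By Margolis × clinic |
|---|---|---|---|---|
| 50% throughout | 70.0% | 90.4% | 90.3% | 90.2% |
| 60 / 20% (75:25) | 67.8% | 86.3% | 90.2% | 89.7% |
| 65 / 47.5 / 25% (40:35:25) | 66.9% | 87.0% | 90.5% | 89.7% |
| 70 / 30% (50:50) | 66.9% | 83.7% | 90.9% | 89.3% |
| 75 / 25% (50:50) | 65.2% | 76.9% | 89.9% | 89.3% |

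Where the strata differ, the loss against stratifying by Margolis is 3.9, 3.5, 7.2 and 13.0 points. Where they do not differ, stratifying costs essentially nothing.

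Type I error in the four scenarios with differing strata is 2.1–3.6% unstratified, 4.1–5.2% by Margolis and 3.9–5.6% by Margolis × clinic.

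**4. Other settings.** A separate set of runs kept the 5.4-fold contrast, with three Margolis levels mixed 60/30/10 or 40/40/20. Power was 83–87% unstratified, 89–91% by Margolis and 88–90% by both factors, with unstratified type I error of 3.2–4.4%. With a milder contrast (relative hazards 1, 0.65 and 0.42) the gain was about 1 point.

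**5. Holding the overall rates instead.** If 50% and 70% (the plan's inputs) are the overall rates, the within-stratum hazard ratio must be about 1.9 to 2.1. In the same four scenarios power is then 93–97% unstratified and 96–99.7% by Margolis.

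**The case against.** - **That the test is unstratified is an inference.** The protocol never uses the word, and this is a condensed article whose analysis plan is not shown. The point stands as a caution. However, the article does more than stay silent: it names the primary test as a two-group comparison, sizes the trial on it and assigns area and duration to secondary analyses. It reads as a choice made.
- **The hazard ratio of 1.74 is an overall effect.** It is derived from overall rates of 50% and 70%. Imposing it within strata lowers the overall aspirin rate to about 65–68%, so the lower power figures depart from the plan's inputs. This stands, and it bars the inference that the trial is underpowered or its sample size wrong.
- **The contrast is assumed.** The Background figures are for 24 weeks and for the extreme groups, the 20 cm² limit truncates the large-ulcer group, and no stratum mix is given. This also stands, so the loss can only be given as a range.
- **The prognostic factors are not ignored altogether.** The secondary Cox analysis adjusts for area and duration and would yield a hazard ratio. That answers any claim that the plan omits them or gives no effect estimate; whether an estimate accompanies the primary test is a reporting detail. The secondary analysis does not decide the primary hypothesis, however, and it omits clinic.
- **Stratifying by clinic as well is not supported on power.** Six clinics by an assumed three levels gives 18 strata for 242 participants, about 13 each. Power is no better than with Margolis alone. This stands and shapes the fix.

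**Conclusion.** The point holds as one of efficiency. The randomisation uses factors that the protocol itself regards as strongly prognostic, and the primary test does not. With assumed 12-week stratum rates and HR 1.74 within strata, the cost is roughly 1 to 8 points of power, and about 13 under the most extreme contrast and mix tried. Type I error is about 2–4% when strata differ.

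A reader might infer that the primary p-value is invalid. It is not: the error is on the conservative side. A reader might also infer that the trial misses its planned power. That follows only if 1.74 is the effect within strata; if the overall rates of 50% and 70% hold, the unstratified test exceeds 90%. Nor does the protocol say that the Margolis index is the strongest predictor known, only that its components predict outcome well.

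**What to change.** Before unblinding, specify the primary test as a log-rank test stratified by Margolis index level. Add clinic only if the resulting strata are not sparse, which can be judged from pooled, blinded counts. Report the hazard ratio and 95% CI from a Cox model stratified in the same way. Keep the unstratified log-rank as a sensitivity analysis.

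If an analysis plan already stratifies the test, it is enough to confirm that and align the protocol wording. The cost is about one sentence of analysis text, with no new data and no change in sample size. This is a free improvement.

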#### Wound pain score

(Baseline and weekly until the wound is healed or to 12 weeks, whichever comes first, and then monthly via phone call until the study completion at 24 weeks): The participants’ self-reported assessments of pain associated with their VLUs in the past week will be measured with an 11-point (0–10) numerical rating scale, where a score of ‘0’ represents no pain, and ‘10’ represents the maximal pain imaginable.

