#### Health-related quality of life and wellbeing index

(Baseline, 12 weeks, and 24 weeks): The EQ-5D is a health-related quality of life and wellbeing instrument. The EQ-5D-5 L is a widely used generic preference-based measure of health outcomes [23]. It consists of a descriptive system together with a visual analogue 0–100 scale. It assesses five dimensions of health – mobility, self-care, usual activities, pain/discomfort, and anxiety/depression. Participants are asked to rate each dimension as one of five levels (no problems, slight problems, moderate problems, severe problems, or extreme problems). This can result in 3125 (5^5^) possible health states, which can be converted to health utilities using nation-specific tariffs, which have been developed for a number of countries [24].

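### Pain is scored up to 15 times after baseline but modelled with one participant random effect; fitted as a plain random intercept, its time-by-group standard error is too small if correlation decays or slopes differ

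*Protocol article*

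**What the plan says.** The section on data management and statistical analyses covers two outcomes in one sentence: "The secondary outcomes of pain score and EQ-5D-5L will be analysed in linear mixed models, with a random effect for participant". The sentence adds "an adjustment for the measure at randomisation" and "an interaction between the time since randomisation and the randomisation group". The sentence before it gives inflammatory markers the same structure and explains that the participant effect is there to handle correlation between a person's repeated values. The article names no random slope, residual correlation or robust standard error. It does not say whether time is linear or categorical, or which contrast will be reported.

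The measurement schedules differ. Pain is scored "Baseline and weekly until the wound is healed or to 12 weeks, whichever comes first, and then monthly via phone call" to week 24; EQ-5D-5L is scored at "Baseline, 12 weeks, and 24 weeks): The EQ-5D is a health-related quality of life and wellbeing instrument". Table 1 agrees with both.

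**The concern.** A random intercept alone assumes that pain at weeks 1 and 2 is no more correlated than pain at weeks 1 and 24, and that everyone in an arm has the same underlying slope. With two post-baseline values this cannot distort the interaction. With up to 15 it can.

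The article's own expectations make equal slopes unlikely. It assumes "Twelve-week survival rates of 0.5 and 0.3 in the placebo and aspirin groups", where survival means still unhealed, so 50% and 70% of ulcers heal by week 12 and the rest do not. If ulcer pain eases as the ulcer closes, individual trajectories will diverge within each arm.

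At stake is a confidence interval for the pain trajectory difference that is too narrow, and so a possible spurious report that aspirin changes pain over time.

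**Working it through.** **Inputs from the article.** Baseline is a covariate, so only post-baseline scores are outcomes. Taking the monthly calls as weeks 16 and 20, the times are weeks 1–12, 16, 20 and 24, so m = 15 for an ulcer that does not heal. The 5% two-sided level is stated for the primary test ("two-sided (alpha = 0.05) test for time to healing") and is assumed here for pain.

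**The plan's own figure.** The article gives no error rate, SD or correlation for pain. Its sample size, used in the simulations below, reproduces: ln 0.3 / ln 0.5 = 1.737, matching "a hazard ratio of 1.74". Freedman's formula gives (1.960 + 1.282)² × (2.737 / 0.737)² = 145 events, and 145 / 0.6 / 2 = 120.8, so 121 per group.

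**Formulas (complete data, linear time, random-intercept fit).** The slope contrast is the difference in mean within-participant slopes. Let c = t − mean(t), S = Σc², V = the true covariance of one participant's 15 scores, I = the identity matrix and J = the matrix of ones. Apart from a common factor for group size, which cancels:

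- true variance = c′Vc / S²
- model-based variance = tr[(I − J/m)V] / [(m − 1)S]
- k = square root of (true / model-based)
- false-positive rate = 2Φ(−1.96 / k)

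Here mean(t) = 138 / 15 = 9.2 and S = 612.4.

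**One case in full.** Assume variance shares of 0.3 stable participant component, 0.5 serial with correlation 0.9 per week, and 0.2 independent error. Then c′Vc = 863.4, so the true variance is 863.4 / 612.4² = 0.002302. The trace is 6.134, so the model-based variance is 6.134 / (14 × 612.4) = 0.000715. Hence k = 1.79 and the rate is 27.5%.

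| Assumed structure | k | False-positive rate |
|---|---|---|
| Exchangeable | 1.00 | 5.0% |
| Serial 0.5; shares 0.4 stable, 0.3 serial, 0.3 error | 1.16 | 9.0% |
| Serial 0.5, no independent error | 1.31 | 13.3% |
| Serial 0.7; shares 0.4, 0.3, 0.3 | 1.31 | 13.3% |
| Serial 0.7, no independent error | 1.61 | 22.4% |
| Serial 0.9; shares 0.3, 0.5, 0.2 | 1.79 | 27.5% |
| Serial 0.9, no independent error | 2.25 | 38.5% |
| Random slopes, SD of 24-week change 0.75 × residual SD | 1.24 | 11.3% |
| Random slopes, 1 × residual SD | 1.38 | 15.7% |
| Random slopes, 2 × residual SD | 2.01 | 32.9% |

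A stable participant component cancels from both variances, so it does not reduce the ratio; independent measurement error does.

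**Simulation (REML, 121 per group, 1,000 runs each).** For serial correlation 0.5, 0.8 and 0.9 without independent error, the rejection rates were 12.9%, 29.9% and 38.1% with complete data. They were 11.8%, 26.5% and 35.2% when weekly scores stopped at healing (60% healed by week 12 in both arms). Exchangeable data gave 4.6% and 4.7%. Participant-clustered robust standard errors on the same fits gave 3.8–5.2% throughout, including the random-slope cases.

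**Without a serial-correlation parameter.** Two further simulations let pain follow healing, with no treatment effect. One rejected in 12.5% of 200 runs, with weekly scores stopped at healing. The other rejected in 17–28% (1,000 runs per scenario, 50% or 60% healed). The pain levels, residual SDs and shape of decline were assumed.

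**Categorical time.** Under the assumed structures, the joint 14-df interaction test gives 5–14%, the week-12 contrast 5–9%, the week-24 contrast 5–19%, and the visit-averaged group difference 5%.

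**Two post-baseline visits.** Put c = (−a, a) and Q = V₁₁ + V₂₂ − 2V₁₂. The true variance is a²Q / (2a²)² = Q / 4a². The model-based variance is (Q/2) / 2a² = Q / 4a². They are equal, so the EQ-5D-5L and biomarker interactions are sound.

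**The case against.** The strongest reply is that the article condenses a fuller plan. A participant random effect does not mean intercept only with independent residuals, and the text excludes neither a serial residual structure nor robust errors. Time coding, covariance and the reported contrast commonly sit in a statistical analysis plan, which is not shown here. This stands to the extent that the error is conditional. It does not remove the point: the article names its device for within-person correlation and applies one structure to a two-visit outcome and a dense weekly series alike.

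A reader might infer that the model necessarily understates the standard error. It does not; under exchangeable correlation the rate is 5%. A reader might also take the upper figures as this trial's error rate. The article gives no SD or correlation for pain, and those figures need linear time, which the mention of time since randomisation may suggest but does not state.

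Fifteen scores is also a maximum. With constant healing hazards matching the assumed rates, the expected number is Σ 0.5^((w−1)/12) over w = 1 to 12, plus 3, or about 12 on placebo. With 0.3 in place of 0.5 it is about 10 on aspirin. Stopping scores at healing reduces the inflation but does not remove it, as the simulations show.

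**Conclusion.** The point holds conditionally. It requires a random intercept with model-based standard errors, together with correlation that decays over time or slopes that differ between participants. The second condition is likely, given the expected mix of healed and unhealed ulcers.

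The linear-slope range of about 9–38% corresponds to assumed weekly serial correlations of 0.5–0.9, and the random-slope cases shown fall within it. It is not a bound: a correlation of 0.3 gives about 7–9%, and 0.95 without independent error gives 44%. For categorical-time contrasts the range is about 5–19%.

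The consequence is confined to pain, a secondary outcome. The log-rank test, the healing and recurrence analyses, and the EQ-5D-5L and biomarker interactions are untouched. The change should be made, but it does not threaten the trial's main conclusion.

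**What to change.** Separate pain from EQ-5D-5L in the analysis text. For pain:

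- State whether time is linear or categorical and which contrast is reported (slope difference, difference at a named week, or difference averaged over visits).
- Fit a participant random intercept and random slope, or a participant effect with a serial residual correlation that respects the unequal spacing of visits.
- Use participant-clustered robust standard errors.

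Robust errors alone restored the nominal rate in the simulations. Modelling the covariance as well is still sensible, because weekly scores stop at healing and estimates from incomplete series depend on the covariance model. A fully unstructured covariance over 15 visits is not a good first choice: it has 15 × 16 / 2 = 120 parameters, with about 242 evaluable participants, many without the later weekly scores.

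The change takes a sentence or two and no new data. Its cost is wider confidence intervals for pain.

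### Part (2) of the secondary adjusted analyses picks covariates by chance imbalance rather than prognosis, with a looser trigger for binary than for quantitative variables, and leaves out wound clinic

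*Protocol article*

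**What the plan says.** Under Data management and statistical analyses, the protocol article states the primary analysis first: "The primary outcome will be analysed with a log-rank test to compare the time to healing", with censoring at 12 weeks. It then plans adjusted work: "A secondary set of analyses will be performed to adjust for two predictors of healing".

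Part (1) is "ulcer area and ulcer duration at baseline". Part (2) is "any baseline characteristics that are found to be imbalanced between the groups to the extent of a 0.25 standard deviation difference in means" for quantitative measures, or "an odds ratio of 1.5 (binary measures"). For time to healing, these adjusted analyses use Cox regression.

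Two other sections bear on the point. Allocation concealment and implementation says that allocation is stratified by wound clinic and by the Margolis index, and describes ulcer size and duration as strongly predictive of outcome. Screening assessment lists the baseline data: age, gender, smoking, ethnicity, employment, medical history and current medication. It gives no prevalences.

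**The concern.** Allocation is randomised, concealed and double-blind, so a difference between groups in a baseline characteristic arises by chance. Its size says nothing about whether the characteristic predicts healing. Part (2) can therefore admit variables unrelated to healing and leave out prognostic ones that happen to be balanced. The sentence introduces both parts as predictors of healing, but nothing in part (2) requires that.

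The two thresholds also look unequal. The sampling error of an odds ratio grows as a characteristic becomes less common, while that of a standardised mean difference does not. Medical history and medication items can be numerous, binary and uncommon, which is where a fixed odds ratio of 1.5 is easiest to reach by chance.

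Wound clinic was important enough to stratify on, yet it is not among the covariates. Part (2) is unlikely to bring it in: stratification is meant to keep clinic balanced, and a factor with six clinics is neither a quantitative nor a binary measure.

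At stake is the make-up of a secondary model. In Cox and logistic models the conditional effect depends on which prognostic covariates are included, so a covariate set decided by chance makes that effect less well defined in advance.

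**Working it through.** **Inputs.** The triggers are 0.25 SD and an odds ratio of 1.5 (Data management and statistical analyses). The odds ratio is read in either direction, as 1.5 or more or 1/1.5 or less, because the group labels are arbitrary. From Sample size: "we require 121 people per group", and "We estimate that 268 participants will be required", which is 134 per group. Prevalences of 5% to 50% are assumptions. Simple randomisation is assumed for variables not used in stratification.

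**The plan's own figure.** The article gives no operating figure for the imbalance rule, but the group size used here can be reproduced. The hazard ratio is ln(0.3)/ln(0.5) = 1.737. Freedman's formula gives 145 events for 90% power. With a mean healing proportion of (0.5 + 0.7)/2 = 0.60, 145/0.60 = 241.7 in total, or 120.8 per group, which rounds up to 121. Adding 10% gives 121 × 1.10 = 133.1, rounded up to 134.

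**Quantitative variable.** The standard error of the standardised difference is √(2/134) = 0.122, so z = 0.25/0.122 = 2.05. The two-sided chance of crossing is 4.1%.

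**Binary variable.** The chance of |ln OR| ≥ ln 1.5 = 0.405 was calculated exactly from two binomial distributions with the same prevalence p. The normal approximation, with SE = √(2/(134·p(1−p))), serves as a check. The standardised difference equivalent to an odds ratio of 1.5 is ln 1.5 × √(p(1−p)).

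| Prevalence | OR 1.5 as standardised difference | Flagged, exact | Flagged, normal approx. | Exact rate ÷ 4.1% |
|---|---|---|---|---|
| 50% | 0.20 | 9.9% | 9.7% | 2.4 |
| 30% | 0.19 | 13.2% | 12.8% | 3.2 |
| 20% | 0.16 | 19.1% | 18.4% | 4.7 |
| 10% | 0.12 | 33.1% | 31.9% | 8.1 |
| 5% | 0.09 | 50.2% | 46.9% | 12.3 |

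The equivalent difference is below 0.25 at every prevalence, so the direction does not depend on the assumed values; only the size does. At 121 per group the picture is the same: 5.2% for a quantitative variable against 10.9% to 52.9% for a binary one.

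**Odds ratio matching the quantitative trigger.** Setting ln OR × √(p(1−p)) = 0.25 gives 1.65 at 50% prevalence, 1.73 at 30%, 1.87 at 20% and 2.30 at 10%. No single odds ratio matches 0.25 SD across prevalences.

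**Number flagged (illustration only).** Take 5 quantitative and 10 binary independent variables; this list is an assumption.
- All binary items at 50% prevalence: 5 × 0.041 + 10 × 0.099 = 1.2 expected. The chance of at least one is 1 − 0.959⁵ × 0.901¹⁰ = 0.71.
- All binary items at 10% prevalence: 5 × 0.041 + 10 × 0.331 = 3.5 expected (3.4 with the normal approximation). The chance of at least one is 1 − 0.959⁵ × 0.669¹⁰ = 0.985.

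**Effect on the estimate.** In 600 simulated trials with 134 per group, 50% against 70% healed, and 5 quantitative and 10 binary covariates unrelated to healing (prevalences 5% to 50%), about 2.4 covariates were flagged on average. Compared with unadjusted Cox regression, adding them raised the standard error of the treatment effect by 1.7% on average (95th percentile 4.1%). The hazard ratio moved by a median of 1.6% (95th percentile about 7%). The mean shift in the log hazard ratio was 0.004.

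**The case against.** The strongest reply is that little depends on this rule. Part (1) is fixed in advance and contains the two factors the article itself calls strongly predictive. The adjusted analyses are secondary. The rule is numeric, stated beforehand and uses baseline data only, so it gives no room for choice driven by outcomes, and it can be applied with coded groups. The simulation shows that non-prognostic extras do almost no harm to the hazard ratio. At 50% prevalence the gap between triggers is modest: 0.20 against 0.25 SD. The larger ratios rest on assumed prevalences. A condensed article may also leave fuller model detail to the analysis plan.

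Most of this stands and sets the severity. It also rules out several stronger readings that a reader might infer:
- That the whole adjusted model is chosen by chance. It is not; only part (2) is.
- That the primary result or its type I error is at risk. The log-rank test uses none of these covariates.
- That the adjusted hazard ratio would be materially biased or imprecise. The figures above do not support this for non-prognostic extras.
- That any disagreement between adjusted and primary results would be due to this rule. Any adjusted Cox model can differ from an unadjusted comparison because the hazard ratio is non-collapsible.

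The reply does not defend the selection criterion itself. The article states the rule explicitly, so this is not detail left to another document. Imbalance remains the wrong basis for choosing covariates, and the two thresholds remain unequal at every prevalence. The simulation does not address prognostic variables omitted because they happened to be balanced.

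**Conclusion.** The point holds for part (2) only, and it is minor. That part adds covariates on chance imbalance without reference to prognosis. At 134 per group its binary trigger fires 2.4 times as often as its quantitative one at 50% prevalence and 12.3 times as often at 5%. The result is a secondary adjusted model whose covariate set depends on chance, may carry non-prognostic variables, omits prognostic ones that are balanced, and does not include wound clinic.

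The expected bias and loss of precision from the extra non-prognostic covariates are small. Part (1) is sound, and the primary analysis, its power and the sample size are unaffected. The flag rates rest on the assumed prevalences and on reading the odds ratio in either direction. The expected number flagged also rests on an assumed list of 15 independent variables.

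**What to change.** Delete part (2). Specify one adjusted model with ulcer area, ulcer duration and wound clinic (as a stratum or a covariate), plus any other baseline variables judged prognostic and named before unblinding. Report baseline imbalances descriptively only.

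The cost is one sentence of analysis wording, with no change to data collection or sample size. The downside is that a large chance imbalance in an unlisted variable could be examined only in a sensitivity analysis labelled post hoc.
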